## Abstract

**Background:**

The majority of retirement village residents are at risk of medication misadventure. In a recent survey of retirement village residents in Victoria, two-thirds had at least one medication-related risk factor, and hence were eligible to receive a government-subsidised Home Medicines Review (HMR). However, only 6% of eligible residents had received a HMR in the previous 12 months. Reasons for the poor uptake of HMR, and interventions for improving HMR uptake, have been identified and developed with input from stakeholders. The trial will test the effect of **P**harmacist-conducted **H**MR to **A**ddress the **R**isk of **M**edication-related **E**vents in **R**etirement Villages (PHARMER) in improving the uptake of HMRs among retirement village residents.

**Methods/Design:**

This is a multicentre prospective cluster randomised controlled trial. Ten retirement villages in Victoria, Australia will be recruited for this trial. Retirement villages will be selected in consultation with the Residents of Retirement Villages Victoria Inc. (RRVV), based on geographical locations (e.g. northeast or southwest), size and other factors. Residents from selected villages will be recruited with the help of RRVV Resident Liaison Officers using a range of strategies. Randomisation will be by geographical location to minimise contamination. Participating villages and residents will be allocated to either Pharmacist Intervention Group (PIG) or Usual Care Group (UCG). Each group will include five retirement villages and will have at least 77 residents in total. The intervention (PHARMER) comprises educating residents regarding HMR, and using a risk assessment checklist by residents to notify their General Practitioners of their medication risk. Uptake of HMR and medication adherence will be assessed in both PIG and UCG at three and six months using telephone interviews and questionnaires.

**Discussion:**

This study is the first to develop and test an intervention to improve the uptake of HMR among Australian residents in retirement villages, with a view to decreasing medication risk. A multi-faceted interventional approach will be used as suggested by stakeholders. The trial is expected to be complete by late 2011 and results will be available in 2012.

**Trial Registration:**

Australian New Zealand Clinical Trials Registry (ACTRN12611000109909)

## Background

Retirement villages offer accommodation for older people who wish to live independently or with limited assistance within a supportive community. There are approximately 1,756 retirement villages in Australia, which accommodate approximately 80,000 residents [1,2]. The number of residents in retirement villages is projected to increase to 300,000 by 2051 [2].

The majority of residents living in retirement villages are at risk of medication misadventure. In our recent survey of 2,116 retirement village residents in Australia, 47% were using multiple medications, and 65% had one or more medication-related risk factors, such as presence of three or more health conditions, use of five or more medications, use of 12 or more medication doses a day, use of medications with narrow therapeutic index or recent changes to their medication regimen [3]. On average, residents in the survey were using four medications [3]. A previous study found that 41% of retirement village residents were using multiple medications including potentially inappropriate combinations, confirming that residents in retirement villages are at risk of medication misadventure [4].

The Australian Pharmaceutical Advisory Council, the National Prescribing Service and the Pharmacy Guild of Australia currently recommend medication reviews to be conducted annually for people who are at risk of medication misadventure [5-7]. Home Medicines Review (HMR) is a government-subsidised medication management review service that aims to optimise medication use and health outcomes for individual patients living in the community [8]. There is no charge to the patient, and both general practitioners (GPs) and pharmacists are reimbursed by Commonwealth Government for providing HMR [8]. HMR is a GP-initiated service conducted by a pharmacist who is accredited to undertake medication reviews.

The 65% of residents who had at least one medication-related risk factor in our survey would meet the eligibility criteria for a HMR [3]; however, only 6% of these at-risk residents had received a pharmacist-conducted HMR in the previous 12 months, despite the fact that the majority (94%) had regular visits to their GPs [3].

The reasons for the poor uptake of HMR among retirement village residents have been investigated by our team, and interventions for increasing the uptake of HMR in this group have been developed with input from stakeholders including retirement village residents, medical, pharmacy and allied health professionals [9]. A multi-faceted interventional approach targeting residents and their health professionals, such as educating residents regarding their risk factors and benefits of HMR, and notifying GPs of residents at risk of medication misadventure using a risk assessment checklist, have been recommended by stakeholders to increase the uptake of HMR in retirement village residents [9].

The **P**harmacist-conducted **H**MR to **A**ddress the **R**isk of **M**edication-related **E**vents in **R**etirement Villages (PHARMER) trial aims to test the effectiveness of a new multi-component intervention delivered by a pharmacist to increase the uptake of HMR among retirement village residents (primary aim), and to improve residents' adherence to medications (secondary aim). The hypothesis is that residents receiving the intervention are more likely to receive a HMR compared to their counterparts receiving usual care, leading to higher HMR uptake at three and six months from baseline.

## Methods/Design

### Study design

The PHARMER trial is a multi-centre prospective cluster randomised controlled trial (RCT).

### Study setting

Ten retirement villages within Victoria, Australia will be recruited for this trial.

### Identification and selection of retirement villages

Retirement villages eligible for the study, such as those with a representative officer (also known as Resident Liaison Officer [RLO]) from the Residents of Retirement Villages Victoria Inc. (RRVV) [10], will be identified in consultation with an officer of the RRVV. Eligible retirement villages meeting the study criteria will be identified by RRVV from their member database. Using the list provided by RRVV, a convenience sample of ten retirement villages will be selected for the study based on the following factors:

• having at least 100 units;

• having at least 20 residents who are members of RRVV; and

• geographical location (northeast and southwest regions).

The two geographical locations will be used to avoid potential contamination (see cluster randomisation). The geographical locations (northeast or southwest) will be randomised to intervention group (Pharmacist Intervention Group [PIG]) or control group (Usual Care Group [UCG]). Each group will include five retirement villages and will have at least 15 km between the PIG and UCG retirement villages. Selected villages should have at least 20 RRVV members to enhance recruitment of participants.

### Recruitment of retirement villages

The RLOs of selected retirement villages will be asked to assist in recruiting their village for the study by facilitating the investigators' approach to each village manager for permission to carry out the study in their village. If a selected village's RLO is unable to assist, another retirement village will be selected and its RLO will be approached. This process will continue until 10 RLOs and their retirement villages are recruited for the trial. Written permission will be obtained from each village manager at the time of recruitment of each village.

### Cluster randomisation

Randomisation to either PIG or UCG according to geographical location (northeast or southwest) will be carried out by an independent person, using a simple randomisation technique (e.g. pick of an envelope) at the completion of retirement village recruitment. Randomisation by geographical locations of facility rather than individual residents or individual retirement villages will be used to minimise any potential contamination from sharing of information between residents belonging to different study groups, or from the same health professionals being involved in the care of residents from both groups.

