### Recruitment of participants

Participants will be residents living in participating retirement villages, recruited with the help of RLOs and village managers. Residents will be recruited using a range of strategies, which include:

• distributing invitation forms to all residents in each village;

• displaying a poster on the notice board or in the common area of each village; and

• advertising the study in the villages' newsletters and/or on the villages' multi-screen televisions (where available).

Residents who are interested in the study will be asked to complete the invitation form and return it to the study investigators using a provided reply-paid envelope, or to contact the study investigators. The invitation form includes questions that ask for the resident's name and contact details, and assess their eligibility for participating in the study. Returned invitation forms will be used to identify and select residents who are eligible for the study. Eligible residents will be invited to participate in the study over telephone. Those who are interested in participating after this initial discussion will be sent a plain language statement, a consent form and a questionnaire. They will be asked to complete the consent form and questionnaire, and return them to the investigators. Once written consent is obtained, eligible residents will be enrolled in the trial and allocated to either PIG or UCG depending on the location of the retirement village they live in.

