### Study timeline

Ethics approval: December 2010

Trial commencement: January 2011 (recruitment of RLOs and retirement villages)

Recruitment of participants and baseline data collection: February - March 2011

Implementation of interventions: April - June 2011

Three-month follow up: September 2011

Six-month follow up: December 2011

Data analysis: January - February 2012

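### The two regions are drawn before any resident is recruited, with no stated concealment from recruiters; drawing after consent and baseline would prevent selection by known arm at little cost

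*Protocol article*

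**What the plan says.** Under *Identification and selection of retirement villages*, "The geographical locations (northeast or southwest) will be randomised to intervention group" or control, five villages to each. Under *Cluster randomisation*, the draw "will be carried out by an independent person", "using a simple randomisation technique (e.g. pick of an envelope) at the completion of retirement village recruitment".

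*Recruitment of participants* describes what happens to residents. Invitation forms go to everyone in each village. Completed forms come back to the investigators, who use them to pick out eligible residents. Then "Eligible residents will be invited to participate in the study over telephone", and only after that conversation are the consent form and baseline questionnaire posted. Liaison officers and village managers help throughout. After written consent, a resident is enrolled and "allocated to either PIG or UCG depending on the location of the retirement village they live in".

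*Study timeline* puts village recruitment in January 2011, followed by "Recruitment of participants and baseline data collection: February - March 2011" and then "Implementation of interventions: April - June 2011".

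The only blinding mentioned is in *Six-month follow up*, and it covers data collection at three and six months.

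**The concern.** In a cluster trial the arm of a cluster should, where possible, be unknown to those who enrol its members. Otherwise the choice of who is selected, how persistently they are telephoned and how the study is put to them can differ by arm.

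Several steps here leave room for that. Eligibility includes expecting to see the GP within three months and being free for an education session, and both depend on what the resident is told. The primary outcome, receiving an HMR, depends partly on the resident's readiness to raise it with the GP, and that readiness can be selected for on the telephone. It is not among the baseline items listed, so a comparison of baseline characteristics would not reveal it. The planned Chi-square comparison of uptake would carry any such imbalance straight into the primary result.

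Baseline adherence and quality of life are self-reported in the same period, with missing answers obtained by telephone. They could be coloured in the same way, which would affect mainly the adherence and SF-12 comparisons.

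**Working it through.** **Order of events**

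1. Villages recruited: January 2011 (*Study timeline*).
2. Regions drawn: when village recruitment is complete (*Cluster randomisation*). The timeline does not date the draw itself; its place follows from reading the two sections together.
3. Residents invited, selected, telephoned, consented and assessed at baseline: February to March.
4. Interventions: April to June.

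The draw thus falls between steps 1 and 3, although nothing uses its result until step 4. With two regions and two arms, one envelope reveals the arm of every village. The allocation placed after consent in *Recruitment of participants* depends only on village location, so it applies the earlier draw and adds no concealment.

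**Sample size (to see whether moving the draw affects it)**

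Inputs from *Sample size*: 3% versus 20%, 80% power, two-sided alpha 0.05. The pooled-variance formula without continuity correction gives 55 per arm, as stated (power at 55 is 0.807). The allowances give 55 × (1 + 0.20 + 0.20) = 77, also as stated. Neither figure depends on when the envelope is drawn.

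**Possible size of the bias (assumed inputs; the article gives none)**

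Let *d* be the excess share of HMR-motivated residents among intervention recruits, and *q* their uptake without any intervention, with 3% uptake in other residents. With no true effect, the spurious difference is *d* × (*q* − 0.03):

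| *d* | *q* | Spurious difference | Share of the 17-point target |
|---|---|---|---|
| 0.10 | 0.10 | 0.10 × 0.07 = 0.7 points | 4% |
| 0.20 | 0.15 | 0.20 × 0.12 = 2.4 points | 14% |
| 0.30 | 0.20 | 0.30 × 0.17 = 5.1 points | 30% |

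A second set of assumptions has 55 analysed per arm, no true effect, and HMR-prone residents making up 30% of the control arm and 40%, 50% or 60% of the intervention arm. The difference is (intervention share − 0.30) × (uptake in prone − uptake in others). The rejection rates use the normal approximation and ignore clustering.

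| Uptake, prone vs others | Difference at 40 / 50 / 60% | Two-sided rejection rate (nominal 5%) |
|---|---|---|
| 8% vs 1% | 0.7 / 1.4 / 2.1 points | 5.5 / 6.7 / 8.5% |
| 15% vs 1% | 1.4 / 2.8 / 4.2 points | 6.1 / 9.1 / 13.4% |

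The approximation is coarse, because 3% of 55 is 0.03 × 55 = 1.65 expected control events. As a check, I summed the binomial probabilities of every pair of event counts (55 per arm) for which the uncorrected Chi-square exceeds its 5% critical value. At the largest imbalance this gives 7.1% in the first row, against 3.3% with no imbalance, and 12.6% in the second, against 4.5%. The picture is the same: small to moderate inflation.

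**The case against.** The strongest reply is that recruiters' awareness of the arm is inferred from silence. An independent person makes the draw, and enrolment and allocation are described as following consent. That is compatible with the result being withheld until then, and a fuller protocol may say so. This stands as far as it goes: a reader might infer that the investigators will know the arm when they telephone, but the article does not say that. It says only that the draw comes first, and it states no concealment.

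There are also safeguards. Invitations go to all residents, residents put themselves forward, and one set of eligibility criteria applies to both arms, including availability for an education session. Uptake is verified with the GP or pharmacist where possible, and follow-up data are collected blind. These points narrow the room for bias, and the last two protect measurement of the primary outcome. None of them hides the arm while residents are being selected, telephoned and consented.

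A reader might also infer that the early draw destroys resident-level comparability that a later draw would restore. That goes too far. With one region per arm, arm and region are confounded whenever the envelope is opened, and a later draw leaves that in place.

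Finally, a later draw is not free. One draw serves all ten villages, so the slowest village could hold up every session, and the timeline has no gap between March and April. That is a fair practical point, which a fixed cut-off answers.

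**Conclusion.** The point holds as a matter of sequence. The article fixes the draw before residents are recruited and assessed at baseline, one draw settles every village's arm, and no concealment from recruiters is stated. Recruitment and baseline self-reports could therefore be influenced by knowledge of the arm.

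How much is unknown. The range of 0.7 to 5.1 points rests wholly on assumed imbalances and uptakes, and its upper end combines the extreme value of both. Against the planned 17 points this is small to moderate, so the documents do not support a claim that the bias alone could produce the anticipated effect. The change is still worth making before recruitment begins, because bias from who was enrolled cannot be reliably removed in the analysis and avoiding it costs little.

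**What to change.** Amend *Cluster randomisation* and *Recruitment of participants*, and date the draw in *Study timeline*:

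- The independent person draws the envelope only after signed consent forms and baseline questionnaires, including answers chased by telephone, are back from all ten villages, or at a fixed end-of-March cut-off, just before the April interventions.
- State how residents whose papers arrive after the cut-off are handled. Confirm before the draw that each region has reached its target of at least 77.
- Use the same recruitment materials and telephone approach in every village. Word them with care: a full account of the HMR education could prompt requests for HMR among control residents, and the design is meant to avoid contamination.

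If the draw has to stay where it is, the weaker alternative is to state that the independent person withholds the result from investigators, liaison officers and managers until consent and baseline are complete.

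**Cost.** Education sessions can be booked only after the draw; the April to June window leaves room for this. The 55 and 77 per arm are unchanged, and the contamination argument is unaffected because it concerns the unit of randomisation and not its timing. The confounding of arm with region remains and needs separate treatment.

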### Sample size

The sample size required for this study was calculated based on the HMR uptake in the previous 12 months (6%) reported in our recent survey [3]. From this figure, we anticipate the uptake of HMR in the UCG to be 6% after 12 months, 3% after 6 months and 1.5% after three months. To demonstrate that the intervention increases the uptake of HMRs from 3% (in the UCG) to 20% (in the PIG) at six months (considered to be a relatively conservative but clinically meaningful increase), with 80% power and a two-sided alpha value of 0.05, 55 participants will be required in each group (total of 110 participants). Allowing for 20% drop-out or loss to follow-up, and 20% for clustering effects, at least 77 participants will be recruited into each arm at baseline (total of at least 154 participants).

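### Two regions are randomised by a single draw, so each arm is one randomised unit and the treatment effect cannot be separated from a regional difference

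*Protocol article*

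**What the plan says.** All references are to the Protocol article; no SAP is at hand.

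- Identification and selection of retirement villages: "The geographical locations (northeast or southwest) will be randomised to intervention group" or to control. The reason given is contamination: "The two geographical locations will be used to avoid potential contamination". The same section adds: "Each group will include five retirement villages and will have at least 15 km between the PIG and UCG retirement villages".
- Cluster randomisation: the draw is made "using a simple randomisation technique (e.g. pick of an envelope) at the completion of retirement village recruitment". Villages and residents are expressly ruled out as the unit: "Randomisation by geographical locations of facility rather than individual residents or individual retirement villages will be used".
- Recruitment of participants: residents are "allocated to either PIG or UCG depending on the location of the retirement village they live in".
- Sample size: 55 per arm for 3% versus 20% uptake at six months, raised to 77 for 20% loss and "20% for clustering effects". No cluster level, cluster size or ICC is given.
- Data analysis: uptake is compared between arms with a chi-square test.
- Study design: the trial is labelled a cluster randomised controlled trial. The article does not mention that each arm is a single randomised unit.

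**The concern.** Two regions allocated to two arms give one unit per arm. Any regional difference that affects HMR uptake is then carried in full by the treatment comparison. The Background section describes HMR as started by the GP and carried out by an accredited pharmacist. The Cluster randomisation section gives shared health professionals as a reason for separating the arms by region. Local provider practice is therefore a direct rival explanation for the primary outcome. The article does not say that practice differs between these two regions, but the design could not detect it or allow for it if it did.

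What is at stake is whether a significant result can be attributed to the intervention. The label of cluster trial and the allowance for clustering suggest that the matter has been dealt with. The planned chi-square test treats residents as independent, so it takes no account of variation between villages or between regions.

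**Working it through.** **1. The plan's own figure.** Pooled-variance formula, two-sided alpha 0.05, 80% power, 3% versus 20% (mean 11.5%):

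n = [1.96·√(2·0.115·0.885) + 0.8416·√(0.03·0.97 + 0.20·0.80)]² / 0.17² = 54.1, so 55 per arm. Inflation: 55 × (1 + 0.20 + 0.20) = 77. Both stated figures reproduce, so this is not an arithmetic error. They rest on resident-level variance plus 20%.

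**2. What the allocation supports.**

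| Design | Possible allocations | Smallest two-sided randomisation p |
|---|---|---|
| As planned: 2 regions, 1 per arm | 2 | 2/2 = 1.0 |
| Villages within region: five per region, split 3:2 and 2:3 | 2 × C(5,3) × C(5,2) = 200 | 2/200 = 0.010 |

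As planned, between-unit degrees of freedom are 2 − 2 = 0. More residents, or more villages in the same two regions, leave this at zero.

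**3. What the 20% allowance covers.** Design effect = 1 + (m − 1) × ICC = 1.2, so ICC = 0.2/(m − 1).

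- Village as cluster: m = 55/5 = 11 gives 0.2/10 = 0.020; m = 77/5 = 15.4 gives 0.2/14.4 = 0.014.
- Region as cluster: m = 55 gives 0.2/54 = 0.0037; m = 77 gives 0.2/76 = 0.0026. That is about 0.003.

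The article does not say which level is meant. On either reading the allowance concerns precision; it does not remove a region effect that coincides with treatment.

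**4. Type I error of the planned test.** Both arms are set at the protocol's 3% control rate with no treatment effect. Analysed per arm: 77 × 0.8 = 61.6, about 62. Region rates are drawn from a beta distribution and events from a binomial, with 200,000 runs. The region ICCs are assumptions, as the article gives none. Region SD = √(ICC × 0.03 × 0.97).

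| Assumed region ICC | Region SD (points) | Rejections at nominal 5% |
|---|---|---|
| 0 | 0 | 3.7% |
| 0.005 | 1.2 | 6.1% |
| 0.01 | 1.7 | 8.5% |
| 0.02 | 2.4 | 12.7% |
| 0.05 | 3.8 | 20.2% |

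**5. How small a difference is declared significant.** With 62 per arm, 2 versus 8 events (3% versus 13%) has pooled rate 10/124 = 0.0806. Chi-square = (6/62)² / (0.0806 × 0.9194 × 2/62) = 3.92, above 3.84. The test can therefore succeed at about 10 points, well short of the planned 17.

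**6. Could region alone give 17 points?** By normal approximation at a 3% base rate, the SD of the difference is √(2·0.03·0.97/61.6 + 2τ²). For an assumed region SD τ of 2, 3 or 5 points this is 0.042, 0.052 or 0.077. Then 0.17 divided by it is 4.07, 3.24 or 2.20, with two-sided probabilities of about 0.005%, 0.1% and 3%. The approximation is rough at so low a rate, and a 5-point SD around 3% implies an ICC near 0.09 (0.0025/0.0291). The order of magnitude is what counts.

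**The case against.** The strongest defence is that regional allocation is deliberate and reasoned. The intervention works through the residents' own GPs, and residents may share information, so separating the arms geographically guards against a real dilution of the effect. That reason stands, and it makes the choice a trade-off rather than an oversight. It does not supply replication, and the article does not state the price paid.

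A second defence is that an unseen SAP may handle clustering. A SAP could bring in village-level variation or covariate adjustment, and adjustment might reduce the confounding. No model can estimate a region effect that is identical to treatment, so this is not a matter that a later document can settle.

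Third, a reader might infer that any positive result would be just a regional difference. The documents do not support that. They give no evidence that uptake differs between the two regions, and step 6 shows that the planned 17-point gap would be hard to produce by region alone. A reader might also infer that the clustering allowance covers an ICC of only about 0.003. That holds only if the region is taken as the cluster; at village level it covers about 0.014 to 0.02.

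Fourth, village-level randomisation may not be practicable. The current rule, "will have at least 15 km between the PIG and UCG retirement villages", concerns only pairs in opposite arms whose regions already differ. Nothing in the article shows that the RRVV list holds enough suitable villages far enough apart within a region, or that distance alone prevents sharing of health professionals. This stands, and it is why a fallback is needed.

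**Conclusion.** The point holds. That there is one randomised unit per arm, with zero between-region degrees of freedom and full confounding of treatment with region, follows from the article's own wording and needs no outside figure. The envelope is only an example, but any simple randomisation of two regions is one binary draw. The five villages per arm inform on variation within a region; they do not replicate what was randomised.

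The size of the damage depends on a between-region variance that the article does not give. Across assumed ICCs of 0.005 to 0.05, the nominal 5% test rejects a true null in about 6% to 20% of trials. The exposure is mainly for significant differences smaller than planned. The finding does not show that the intervention effect would be spurious, and it does not make geographical separation wrong in itself. It shows that the allocation cannot support the planned 5% test as a randomisation-based test of the intervention.

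**What to change.** **Preferred, before village recruitment.** Select villages so that units in opposite arms can be at least 15 km apart, treating nearby villages as one unit. Randomise these units within northeast and within southwest so that both arms are present in both regions, and analyse at the level of the randomised unit. With five separate villages per region split 3:2 and 2:3, this gives the 200 allocations in step 2; merging villages lowers that number.

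Cost: a revised selection list, several allocations instead of one, and intervention visits in both regions. The 15 km rule then applies to more pairs of villages, feasibility from the RRVV list is unknown, and some risk of shared health professionals remains.

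**If not feasible.** Keep the regional allocation, but state in the protocol and the report that there is one randomised unit per arm, that region is confounded with treatment, and that p-values are conditional on no regional difference. Do not present the result as a cluster-randomised estimate of effect. This costs wording only, but it narrows what the trial can claim.

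In either case, state the level and the ICC that the 20% clustering allowance assumes.
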